#### Month 6 Visit

This last visit will be devoted to the collection of follow-up data at 6 months (medico-sportive evaluation and administration of questionnaires). If patients do not attend this follow-up visit, a de-identified questionnaire will be sent to the patients' homes within 2 weeks in a pre-stamped, stamped envelope addressed to CIC-1433 EC.

A random selection of 10 patients, 5 from each intervention group, will be contacted by phone to obtain their agreement to participate to the qualitative investigation. An appointment will be made for a retrospective narrative interview at their convenience. It will enable the participants to question their experiences, difficulties and levers, as well as the adaptations made to the programme, in order to identify the indicators of effectiveness and the adaptations necessary for adherence and greater effectiveness of the programme. This interview will be carried out face-to-face by a researcher from the project team.

Two semi-structured interviews of the 2 fencing master will be carried in order to assess the effectiveness indicators, in particular the acceptability of the patients (profiles remaining committed), the difficulties encountered (technical, social, psychological, etc.), the levers (posture, resources, support) and the necessary adaptations (pedagogy, gestures, technique) for better commitment and effectiveness.

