### Recruitment and Randomization

The study is to be initiated from September 2021 with an anticipated end for subject recruitment in November 2021. Study completion is scheduled for June 2022.

The study will be proposed to the patient by the oncologist or surgeon after surgery. If interested, the patient will be referred to a sports physician for a medico-sportive evaluation. At the end the evaluation, if the patient meets the inclusion criteria, she will be randomly assigned to one of the 2 groups based on a 1:1 principle using automatic software Ennov^®^ (Figure 1):

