### Interventions

Once a week, for a duration of 1–1.5 h/session, and during a complete sport season, a group of 10–12 patients practiced adapted fencing. Following a warm up time dedicated to muscle awakening and progressive cardio-respiratory solicitation, patients then started specific fencing exercises from fundamental footwork (advance, retreat, lunge) to actions involving the injured side that holds the saber. Fencing is adapted in so far as all offensive and defensive actions are performed with respect of the mobility of the shoulder. Primary (tierce = outside; quarte = inside; quinte = head) and secondary parries are therefore executed by patients with the highest mobility but without ever causing pain. Coordination, agility and strength are trained during exercises between patients and during lessons with the fencing master. The adapted fencing session finished with a cool down period and a final salute.

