#### Month 3 Visit

For patients of the DRG, it will confirm the absence of contraindications to the practice of fencing before the beginning of the sessions within 8 days. At the end of this visit, medical data such as complementary treatments (pain treatment, anti-diarrhea, antiemetic's, psychotropic drugs, treatment not declared to the doctor), weight gain, presence of lymphedema, co-morbidities and patient-reported outcomes will be collected for all patients whatever the intervention group. An appointment for the visit at 6 months will be offered to each patient regardless of the group.

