### Sample Size

The 2 fencing halls have a maximum capacity of 24 patients per year (12 patients per hall). The results of this pilot study will be used to refine the number of subjects needed for the main clinical trial. Nevertheless, with the number of patients to be included, setting an alpha risk of 5%, a power of 80% and assuming normality of the distribution of the QoL score with a standard deviation of 10 points, we will be able to detect a minimum difference in QoL evolution of 8.26 points between the two groups.

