#### Qualitative Analysis

A thematic analysis of the interviews with patients and masters of arms using NVivo^®^ software will make it possible to describe the appropriateness of the intervention to the realities of the field and the needs of the target population. An automatic speech analysis (detection of verbal recurrences, etc.) will also be carried out using the ALCEST^®^ software.

A cross-check between what the fencing masters say and what the patients say will make it possible to identify the key components of the programme and the areas for improvement. A cross-reference between the patients' discourse and the results on quality of life will be carried out, in an attempt to qualitatively document the evolution. The acceptability of the programme will be evaluated, and the rate of participation/non-participation of patients in each fencing session will be described as a percentage. This will make it possible to estimate the degree of adherence to the intervention.

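### The interviews are meant to explain adherence, but the 10 interviewees are drawn without regard to attendance, and adherence is summarised per session rather than per patient

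*Protocol article*

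**What the plan says.** Under Month 6 Visit, the patient interviews are set up as follows: "A random selection of 10 patients, 5 from each intervention group, will be contacted by phone to obtain their agreement". Of the interview itself the section says: "It will enable the participants to question their experiences, difficulties and levers, as well as the adaptations made to the programme". It adds that the aim is to find the changes needed for adherence and for a larger effect. Neither this section nor Qualitative Data selects on attendance or on stopping.

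The same section plans interviews with the two fencing masters, "in particular the acceptability of the patients (profiles remaining committed), the difficulties encountered (technical, social, psychological, etc", and asks them also about the adaptations needed.

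Under Qualitative Analysis, adherence is to be estimated thus: "the rate of participation/non-participation of patients in each fencing session will be described as a percentage".

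Other sources cover every patient. Under Month 3 Visit, complementary treatments including pain treatment are recorded, and "presence of lymphedema, co-morbidities and patient-reported outcomes will be collected for all patients whatever the intervention group". Month 6 brings a medico-sportive evaluation and questionnaires, with a postal questionnaire for patients who do not attend. The instruments under Patient Reported Outcomes cover pain, breast and arm symptoms, treatment side effects and arm disability.

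**The concern.** The question put to the interviews is partly about adherence, but the sampling ignores adherence. Patients who stopped, or who came rarely, can speak most directly about what would have kept them in the programme. In a trial of 24 they may number only one or two per arm, and a simple random draw can then miss them all.

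The attendance summary does not fill the gap. A percentage for each session describes the session, not the patient. It cannot separate a few patients who left from many who each missed some sessions, and those two patterns call for different changes to the programme.

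The Introduction and the Conclusion present this as a pilot whose findings will shape the programme and a larger trial. If the interviews happen to include only regular attenders, the adaptations carried forward would rest on patients for whom the programme already worked well enough to continue.

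**Working it through.** The plan gives no figure on this point, so there is none to reproduce.

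**Inputs**
- Total of 24 patients (Abstract; Sample Size gives the same number as the capacity of the two halls).
- Allocation: "randomly assigned to one of the 2 groups based on a 1:1 principle" (Recruitment and Randomization), taken here as 12 per arm.
- Interviews: 5 drawn at random per arm (Month 6 Visit), assumed to be drawn from all 12.
- Patients who stop: not given in the document. Values of k = 1, 2 and 3 per arm are assumed.

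**Chance for one patient.** She is drawn with probability 5/12 = 41.7% and not drawn with probability 7/12 = 58.3%.

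**Chance for k stoppers in one arm** (hypergeometric)
- None drawn: C(12−k, 5) / C(12, 5), with C(12, 5) = 792.
- At least one not drawn: 1 − C(12−k, 5−k) / 792.
- None drawn in either arm, with k stoppers in each: the square of the first quantity, since the arms are drawn separately.

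| k per arm | None drawn, one arm | None drawn, both arms | At least one not drawn, one arm |
|---|---|---|---|
| 1 | 462/792 = 58.3% | 34.0% | 1 − 330/792 = 58.3% |
| 2 | 252/792 = 31.8% | 10.1% | 1 − 120/792 = 84.8% |
| 3 | 126/792 = 15.9% | 2.5% | 1 − 36/792 = 95.5% |

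The both-arms column is the relevant one for the programme as a whole, because both arms receive the same fencing. The one-arm column matters if early and delayed fencing are to be understood separately. If a single patient stops in the whole trial, the chance of missing her is 58.3%.

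**Sensitivity to balance.** If the arms came out 11 and 13, the chance that one given stopper is not drawn would be 6/11 = 54.5% or 8/13 = 61.5%.

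**Attendance summary.** Take 12 patients and 12 sessions, with 50% present at every session. That is 12 × 6 = 72 attendances. It fits 6 patients attending all 12 sessions and 6 attending none (6 × 12 = 72). It fits equally well all 12 patients attending 6 sessions each (12 × 6 = 72). The per-session percentages are the same in both cases; the exposure of each patient is not.

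**The case against.** A reader might infer more than the text supports.

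- **That patients who stop are heard only if drawn, so that stopping for pain or treatment effects goes unseen.** This does not stand. Pain, arm symptoms, arm disability, lymphoedema and treatments are due from everyone, and patients absent at month 6 are sent a questionnaire. What these sources lack is the link between a symptom and the decision to stop.
- **That random sampling is the method least likely to reach them.** This is wrong. The draw gives a stopper the same 5/12 chance as a completer, and interviewing only volunteers or completers would be worse. Agreement to be interviewed is needed under any scheme.
- **That the masters are asked only about patients who stayed.** They are also asked about difficulties, and their accounts are compared with the patients'. They remain an indirect source on why someone left.
- **That the Interventions section promises pain-free sessions.** The words "executed by patients with the highest mobility but without ever causing pain" describe how the parries are adapted. They are not a tolerability result for the interviews to confirm or refute.
- **That reasons for absence are not recorded.** The article does not mention them, but it condenses a fuller protocol that is not shown and may contain such a field. This silence is not counted against the plan.

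It can also be said that random selection is a legitimate choice in a qualitative sub-study, that the risk of missing every stopper falls quickly as stopping becomes more common, and that attendance per patient can be derived from the same records. All of that is fair. It limits the size of the point but does not remove the mismatch between the stated aim and the stated sampling and summary.

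**Conclusion.** The point holds in a limited form. The article states an aim that concerns adherence, a draw that ignores attendance, and an adherence summary that does not show each patient's exposure. Any one stopper has a 58% chance of not being drawn. The chance that the interviews include no stopper at all is 34% with one per arm and 10% with two per arm.

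These figures rest on 12 patients per arm, a draw from all patients in the arm, no refusals, and assumed numbers of stoppers. Refusal by a stopper who is drawn would raise the chance that none is interviewed. The point concerns what the pilot can say about adherence and adaptation; it does not touch the primary comparison of quality of life.

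**What to change.** **Month 6 Visit.** Keep 5 interviews per arm. Reserve up to 3 of the 5 places for patients who stopped fencing or attended fewer than half of their sessions, chosen at random if more than 3 qualify. Fill the remaining places at random from the other patients in that arm. Whenever at least one patient in an arm qualifies, the chance that none is invited falls to zero; refusals remain possible. The cap leaves at least 2 places per arm for regular attenders, whose experience the interviews also seek.

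**Qualitative Analysis.** Alongside the percentage for each session, report the number of sessions attended by each patient out of the maximum of 12, with the main reason for stopping where it is recorded.

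**Cost.** The number of interviews stays at 10. The additions are a per-patient tabulation of attendance and a selection step once attendance is known. The interviewees are no longer a simple random sample, so shares among them should not be read as shares of all 24 patients. A thematic analysis does not need that property.

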### Data Collection

During the study, data on socio-demographic medical and patient-reported outcomes will be collected at each follow-up.

#### Socio-Demographic

Age, marital status, family situation, number of children and their ages, level of education, current professional situation (active or not), socio-professional category, social support and life habits (sleep problems, practice of a physical activity other than fencing,…).

#### Medical

Date of diagnosis of breast cancer, stage of the disease, type of surgery (including lymph node expertise by sentinel procedure or lymph node axillary dissection), type of adjuvant treatment, complementary treatments (pain treatment, anti-diarrhea, antiemetic's, psychotropic drugs, treatment not declared to the doctor), weight gain, presence of lymphedema, co-morbidities.

#### Patient Reported Outcomes

##### Quality of Life

Quality of life will be measured using the EORTC QLQ-C30 and BR23 module. The EORTC (Quality of Life Questionnaire Core 30) questionnaire (“European Organization for Research and Treatment of Cancer”) is a questionnaire developed by Aaronson et al. (1993). It is composed of 30 items and is intended for all patients with cancer, regardless of location. Its psychometric properties were verified in the original version. Patients should answer these questions by circling a number between 1 (“not at all”) and 4 (“a lot”) that best describes their situation at the time of administering the questionnaire. It results in 15 scores of QoL dimensions: physical activities, daily activities, cognitive functions, emotional wellbeing, fatigue, pain, nausea and vomiting, loss of appetite, constipation, diarrhea, financial impact and global health. The QLQ-BR23 questionnaire consists of 23 items to evaluate the symptoms of BC and the side effects of the treatments (Sprangers et al., 1996). It explores 8 different dimensions (4 functional dimensions: body image, sexual activity, sexual pleasure, future perspective and 4 dimensions of symptoms: side effects of treatments, symptoms in the breast, symptoms in the arm and feelings related to the loss of hair). All scores for domains and unique items are linearly transformed from 0 to 100. A high score for the functional domains will express a good functional level, a high score for the general health domain and QoL will translate a good QoL but a high score for areas of symptoms will represent a high level of symptoms. Non-responses are taken into account by assigning them the mean value of the dimension if the number of items to which a response is given is greater than half the items in the dimension. If the patient has not responded to at least half of the questions in the dimension, the score cannot be calculated (missing value).

##### Disability

Disability the DASH (Disabilities of the Arm, Shoulder and Hand measurement tool) (Dubert et al., 2001), is a subjective self-assessment questionnaire for the overall functional capacity of the upper limbs. It evaluates from 30 items the ability to perform 23 activities, the severity of the symptoms and optional sporting or instrumental and professional activity. The entire questionnaire will be administered to the patient. The overall score is in the form of a score on 100 by the following calculation method: [(sum of n responses)−1] / n × 25. A high score indicates a high overall functional disability. The score is valid only if 90% of the questions were filled by the patient (i.e., 3 missing values at most).

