#### Secondary Objectives

(SO1) Compare ERG vs. DRG on the 6-month evolution of several secondary criteria of patients operated for invasive BC: other dimensions of QoL, disability of the lateral arm, fatigue and anxiety-depression.(SO2) Compare early (3-months) effectiveness of fencing (fencing vs. no fencing) on physical and psychological health of patients operated for BC.(SO3) Identify 6-month trajectories of QoL, disability of lateral arm, fatigue and anxiety-depression and theirs associated factors.(OS4) Evaluate retrospectively the conditions of effectiveness of RIPOSTE (qualitative interview).

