#### Outcomes

The primary outcome is the evolution of QoL score. Secondary outcomes are disability score, fatigue, anxiety-depression, cost-effectiveness and process evaluation.

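### The printed DASH formula subtracts 1 from the sum instead of the mean, so, followed literally with items coded 1 to 5, it gives about 24 to 124 rather than a score out of 100

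*Protocol article*

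**What the plan says.** All of the scoring text is in the Disability section of the protocol article, under Patient Reported Outcomes.

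- Scale: "The overall score is in the form of a score on 100".
- Rule: "sum of n responses)−1] / n × 25". The quotation starts just after the opening square bracket and parenthesis. In the article the square bracket encloses both the sum and the −1, and the division by n follows it.
- Items: "It evaluates from 30 items the ability to perform 23 activities".
- Missing items: "The score is valid only if 90% of the questions were filled by the patient (i.e., 3 missing values at most".
- Direction: "A high score indicates a high overall functional disability".

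The section gives no response range for the items, and the article gives no other DASH formula.

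The score has a defined role. The Outcomes section states: "Secondary outcomes are disability score, fatigue, anxiety-depression, cost-effectiveness and process evaluation". The first secondary objective compares the two groups on the six-month evolution of "other dimensions of QoL, disability of the lateral arm, fatigue and anxiety-depression".

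**The concern.** The rule and the scale that introduces it do not agree. Multiplying by 25 turns a range of width 4 into a range of width 100, and subtracting 1 moves the lowest response to zero. Both steps make sense for a mean item response running from 1 to 5. In the printed rule, however, the −1 acts on the total of up to 30 items before the division. It therefore lowers the final score by only 25/n, less than one point, where 25 points are needed.

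The article states this rule in full for a listed secondary outcome, so it is not a detail left to a longer document. An analyst who followed it would report a patient with no disability at about 24. Since higher scores mean more disability, both groups would look more disabled than they are at every visit. The error could also go unnoticed, because many of the wrong scores would still fall between 0 and 100.

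**Working it through.** **Inputs**
- S = sum of the answered items, and n = number of items answered.
- n runs from 27 to 30: 30 items with at most 3 missing (Disability). The two forms of the missing-item rule agree, since 90% of 30 is 27.
- Assumption: items are coded 1 to 5. The article does not say so, and other codings are tried below.

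**Does the printed rule give the stated scale?**
Printed rule: (S − 1)/n × 25.

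With n = 30:
- all items 1: (30 − 1)/30 × 25 = 24.17
- all items 3: (90 − 1)/30 × 25 = 74.17
- all items 5: (150 − 1)/30 × 25 = 124.17

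With n = 27:
- all items 1: (27 − 1)/27 × 25 = 24.07
- all items 3: (81 − 1)/27 × 25 = 74.07
- all items 5: (135 − 1)/27 × 25 = 124.07

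The stated scale is not reproduced.

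**Moving the bracket**
Alternative rule: (S/n − 1) × 25. For every n from 27 to 30, all 1s give 0, all 3s give 50 and all 5s give 100. This matches the stated scale.

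**Size of the shift**
Printed minus alternative = (25S/n − 25/n) − (25S/n − 25) = 25 − 25/n.
- n = 30: 25 − 0.83 = 24.17
- n = 27: 25 − 0.93 = 24.07

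The shift does not depend on the responses or on how they are coded. Its whole range over the permitted n is 25/27 − 25/30 = 0.926 − 0.833 = 0.093 points. That is also the most by which a change from baseline could be distorted, and only if a patient answered 27 items at one visit and 30 at the other. With the same n at both visits the shift cancels exactly.

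**When would a wrong score show itself?**
At n = 30 the printed score passes 100 when the mean response exceeds (100 × 30/25 + 1)/30 = 121/30 = 4.03. Any milder pattern gives a value that looks admissible.

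**Could another coding or reading rescue the printed rule?** (n = 30)
- Coding 0 to 4: −0.83 to 99.17. The lowest score is negative, and the −1 has no purpose.
- Coding 1 to 4: 24.17 to 99.17.
- Dividing by the product n × 25, coding 1 to 5: 0.04 to 0.20.
- Applying 25/n to the 1 alone, coding 1 to 5: 29.17 to 149.17.

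None of these gives 0 to 100.

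**The case against.** The strongest reply is that this is a misplaced bracket in a condensed article. The instrument is published and referenced, the intended scale is stated in the same sentence, and nothing shown indicates how the score is actually programmed. A patient without disability scoring 24, or any score above 100, would reveal the slip. This stands in part: the consequence is conditional on someone following the printed line, and whether anyone has done so is unknown. It does not remove the point, because the article states a complete rule that gives wrong values when followed.

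The second reply concerns what is at stake, and most of it stands.

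- A reader might infer that the comparison of early and delayed fencing on disability is compromised. It is not. Secondary Objectives and Quantitative Analysis rest on evolution over six months, and a nearly constant shift drops out of changes and group differences. The shapes of the planned trajectories are likewise essentially unchanged.
- A reader might infer that the pilot could not inform the main trial. The Sample Size section works from a standard deviation and a difference, and it does so for the quality-of-life score. The shift leaves both quantities essentially intact for the DASH and does not touch quality of life at all.
- A reader might infer that the DASH data would be lost. They would not: subtracting 25 − 25/n recovers the correct score exactly, and the items can be rescored at any time.
- A reader might infer that the trial has no other arm or shoulder measure. The Quality of Life section includes the arm-symptom dimension of the QLQ-BR23. The Inclusion section names the Constant index for shoulder mobility within the medico-sportive evaluation, and the Month 6 Visit section lists that evaluation again, although the Outcomes section does not list the index as an outcome.

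The third reply is that the 1 to 5 coding is inferred. That is correct and should be said openly. The upper end of about 124 depends on it. The 24-point gap between the printed and the rearranged rule does not.

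**Conclusion.** The printed DASH rule contradicts the scale it is meant to produce. With items coded 1 to 5, programming it literally would raise every DASH level by 24.07 to 24.17 points and stretch the top of the scale to about 124. Reported means by group and visit would then not be directly comparable with correctly scored DASH data until rescored.

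The damage is confined to absolute levels. The distortion of a change score is at most about 0.09 points. Group contrasts and the standard deviation are essentially unaffected, and the primary outcome does not use this formula. The documents do not support any claim that the trial's conclusions on disability would be invalid, or that scores have in fact been computed this way. Severity is minor to moderate: a definite error in the rule for a listed secondary outcome, with limited and reversible consequences.

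The conclusion rests on the formula being printed as intended, on n between 27 and 30, and, for the range quoted, on 1 to 5 coding.

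**What to change.** - Replace the formula in the Disability section with [(sum of n responses)/n − 1] × 25, where n is the number of items answered, 27 to 30.
- State the item coding (1 to 5) beside it.
- Confirm that the scoring program uses this form, and rescore from the items if it does not.
- Add a check that every score lies between 0 and 100. As the range check would miss wrong scores for mean responses up to about 4.03, also run two test records: all 1s must give 0 and all 5s must give 100.

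The cost is one line in the document and a short check of the program. No data collection, sample size or analysis model changes.
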